# Does continuous endurance exercise in water elicit a higher release of ANP and BNP and a higher plasma concentration of FFAs in pre-obese and obese men than high intensity intermittent endurance exercise? – Study protocol for a randomized controlled trial

**DOI:** 10.1186/1745-6215-14-328

**Published:** 2013-10-10

**Keywords:** Obesity, ANP, BNP, EPOC, Exercise intensity, Water immersion

## Abstract

**Background:**

Atrial natriuretic peptides (ANP) and Brain natriuretic peptides (BNP) stimulate fat cell plasma membrane receptors. They are potent lipolytic agents on isolated fat cells from subcutaneous adipose tissue. The physiological effects of continuous endurance exercise on ANP release and plasma free fatty acids (FFA) concentrations have been well described. The enhancement of fat metabolism using high intensity intermittent exercise protocols has been assessed in more recent investigations. The combined effects of endurance exercise and water immersion on ANP and FFA plasma concentration and the magnitude of excess post-exercise oxygen consumption (EPOC) might be further enhanced by choosing the most effective exercise protocol. Exercise modalities may play a significant role in the future prevention and treatment of obesity.

**Methods/design:**

The two testing trials will be performed according to a randomized and cross-over design. Twenty healthy sedentary pre-obese and obese class-1 men will be scrutinized with regard to their metabolic responses to continuous exercise in water and to high intensity endurance exercise in water. Both trials will be matched for energy expenditure. After preliminary testing, the tests will be conducted as repeated measurements. The two different exercise protocols will be compared. The aims of the study are to investigate (1) whether continuous endurance exercise or high intensity intermittent endurance exercise in water elicits both a higher release of ANP and BNP and a higher plasma concentration of glycerol and (2) to determine whether continuous endurance exercise in water or a high intensity intermittent endurance exercise in water would lead to a more pronounced short term (two hours) EPOC effect.

**Discussion:**

If our hypothesis would be confirmed, the most effective exercise protocol based on the combined effects of high intensity endurance exercise and water immersion on ANP and BNP release and glycerol plasma concentrations can be identified. Moreover, the magnitude of the EPOC effect can be augmented. Our study would provide a major contribution for creating optimized exercise modalities in the prevention and treatment of obesity.

**Trial registration:**

Current controlled trials, ISRCTN95488515

## Background

Lipolysis of adipose subcutaneous tissue is controlled by a diversity of inhibiting and stimulatory pathways. Catecholamines, natriuretic peptides (NPs) and insulin are considered as the main endocrine related factors in the regulation of lipolysis [1]. In fat cells lipolysis is activated through stimulation of β-adrenergic receptors (ARs) and inhibited through activation of the α_2_-adrenergic receptor [2]. The simultaneous activation of both receptors modulates the intracellular cyclic adenosine monophoshate (cAMP)-dependent protein kinase, leading to the phosphorylation and activation of perilipin and hormone-sensitive lipase [2,3].

Compared to lean subjects, obese subjects seem to have impaired exercise-induced subcutaneous adipose tissue lipolysis [3,4] - in particular obese subjects with insulin resistance or type-2 diabetes. This is mainly attributed to the activation of antilipolytic α_2_-adrenergic receptors during exercise. These α_2_-adrenergic receptors largely outnumber β-adrenergic receptors in subcutaneous adipocytes and α_2_-adrenergic receptors density correlates with fat cell size [2,3]. In obese subjects complete blockade of fat cell receptors, however, does not suppress the exercise-induced lipolysis entirely [1-4]. Other lipolytic pathways thus stimulate lipolysis and contribute to the regulation of lipid mobilization in humans [5].

A growing body of evidence suggests that NPs play a role in the regulation of lipid metabolism via the control of adipose tissue lipolysis [6]. Atrial natriuretic peptides (ANPs) stimulate fat-cell plasma membrane receptors bearing intrinsic guanylylcyclase activity and increase intracellular levels of cyclic adenosine monophosphate (cGMP), which activates a cGMP-dependent protein kinase (PKG). ANPs are potent lipolytic agents on isolated fat cells from subcutaneous adipose tissue [3]. Thus, the ANP-dependent lipolytic pathway appears to be involved in the enhancement of lipolysis in subcutaneous adipose tissue and is responsible for the residual mobilization under adrenergic receptor blockade [3]. The fall in plasma insulin during exercise could also contribute to the enhancement of lipolysis due to the reduction of its antilipolytic effect.

The ability of mammals to resist weight gain and body fat accumulation is very closely tied, both genetically and pharmacologically, to the capacity to expand the number and activity of brown adipocytes within white fat depots, and, in most cases, this is also correlated with improved blood glucose levels, insulin sensitivity, and body composition [7]. The conversion of white to brown-like adipocytes operates under physiological conditions in humans; NPs could be included in the list of factors contributing to the physiological control of energy dissipation. [8].

In addition, the very recent demonstration that NPs increase oxidative capacity and energy uncoupling in human skeletal muscle opens interesting perspectives. [8]. Activation of NP signaling in human skeletal muscle enhances mitochondrial oxidative metabolism and fat oxidation. NP could contribute to exercise training-induced improvement in skeletal muscle fat-oxidative capacity in humans [9]. Ideally, NP signaling in skeletal muscle, enhanced by exercise, may trigger favorable metabolic adaptations to increase fat oxidation, alleviate lipotoxicity, and enhance insulin sensitivity [8]. Chronic upregulation of adipose tissue NP receptor type C (NPR-C) expression may increase NP clearance, reduce circulating NP levels, and contribute to obesity-related cardiovascular and metabolic disorders. The potential relevance of insulin-induced upregulation of NPR-C on circulating NP levels in humans is still unclear and needs to be investigated in further long-term observations [8].

Endurance training improves ANP as well as beta-adrenergic-receptor-mediated lipid mobilization in the subcutaneous adipose tissue of obese subjects [1-4]. The physiological effects of continuous endurance exercise on ANP release and plasma free fatty acid (FFA) concentrations have been well described [1,3]. The further enhancement of fat metabolism using high-intensity intermittent exercise protocols has been the focus of more recent investigations [10-13]. High intensity intermittent exercise provides more potent metabolic stimuli, leading to increased lactate and catecholamine levels. The accompanying rise in plasma glycerol concentrations suggests that fat stores may supply a significant amount of energy during this form of exercise [13]. Investigations have shown that circulating ANP concentrations increased 2- to 3-fold during short exercise bouts of increasing intensities [10]. ANP may act as a relevant physiological agent controlling exercise-induced lipolysis in endurance exercise consisting of repeated bouts [3,14]. The magnitude of the excess post-exercise oxygen consumption (EPOC) effect is also dependent on the type of the preceding exercise protocol. A curvilinear relationship between the magnitude and the intensity of the exercise bout has been reported [15].

Water immersion attenuates adrenaline and noradrenaline and augments ANP release during exercise [16]. Even though water immersion blunts exercise-induced sympatho-adrenal activation, lipid mobilization and lipid oxidation rates are maintained or even improved [16]. Free fatty acid concentrations are increased; glucose and lactate measurements are decreased [16]. The combined effects of endurance exercise and water immersion on ANP and FFA plasma concentration and the magnitude of EPOC might be further enhanced by choosing the most effective exercise protocol. Exercise modalities may play a significant role in the future prevention and treatment of obesity.

The first aim of this study is to investigate whether continuous endurance exercise or high-intensity intermittent endurance exercise in water elicits both a higher release of ANP and a higher plasma concentration of FFAs. The second aim is to determine if continuous endurance exercise in water or high-intensity intermittent endurance exercise in water leads to a more pronounced short term (that is, 2 hours) EPOC effect.

## Methods

### Trial design

The two testing trials will be performed according to a randomized crossover design. Subjects will be allocated to one of the two intervention groups according to a prepared randomization list and will at this time be unaware of group to which they are allocated. Implementation of the random allocation sequence will be done via central telephone to provide allocation concealment. The flow chart of the study is described in Figure 1.

**Figure 1 F1:**
[figure not shown]
Trial design.

### Participants

Eligible participants will be recruited via advertisements on the websites and magazines such as *FIT FOR LIFE* and *Schweizerische Adipositas-Stiftung*. A sample of 20 healthy sedentary pre-obese and obese class-1 men with a body mass index (BMI) ranging from 30.0 kg/m^2^ to 34.9 kg/m^2^ according to the World Health Organization (WHO) 2004, will be scrutinized with regard to their metabolic responses to continuous exercise in water and to high-intensity endurance exercise in water. Participants will be informed about potential risks and the trial process both verbally and in written form. Ethical approval and consent was obtained by the Ethics Committee in St. Gallen, Switzerland.

### Inclusion criteria for participants

The inclusion criteria are: male gender (differences in estrogen concentrations between men and woman result in greater reliance on fat oxidation during exercise in women; between the different phases of the female menstrual cycle substrate utilization also varies); BMI between >30.0 kg/m^2^ and <34.9 kg/m^2^; age >18 years and <50 years; verbal and written information of the participants, signed declaration of consent; and no cardiovascular risk (completion of the Physical Activity Readiness Questionnaire (PAR-Q)).

### Exclusion criteria for participants

The exclusion criteria are: female gender; cardiac insufficiency >New York Heart Association (NYHA) stage 1; continuous arrhythmia; respiratory obstruction; high blood pressure ( >140/90 mmHg); BMI <30.0 kg/m^2^ and >34.9 kg/m^2^; age <18 years and >50 years; any medication; or signed declaration of consent missing.

### Intervention

The aims of the study are to investigate (1) whether continuous endurance exercise or high-intensity intermittent endurance exercise in water elicits both a higher release of ANP and BNP and a higher plasma concentration of glycerol, and (2) to determine if continuous endurance exercise in water or high-intensity intermittent endurance exercise in water leads to a more pronounced short term (that is, 2 hours) EPOC effect.

### Overview

Twenty healthy sedentary pre-obese and obese class-1 men with BMI ranging from >30 kg/m^2^ to <34.9 kg/m^2^ according to WHO 2004, will be scrutinized with regard to their metabolic responses to continuous exercise in water and to high-intensity endurance exercise in water. Both trials will be matched for energy expenditure. After preliminary testing, the tests will be conducted as repeated measurements, with 72 hours of separation time in between. The two different exercise protocols will be compared.

### Environmental conditions and preparation of the subjects

All trials will be conducted under standardized environmental conditions in regard to the temperature of air and water (that is, the thermoneutral zone on land between 23°C and 26°C at a relative humidity of 60 to 70%, equivalent to a water temperature of 28°C). Participants will be tested at 8 am after an overnight fast following a standardized two-day diet and will be asked to refrain from any physical exercise on the day before testing. Prescription drugs will be recorded.

### Preliminary testing

Maximum voluntary ventilation (MVV) and forced expiratory volume (FEV_1_) will be assessed initially. The ventilatory threshold 2 (VT2) as defined by Wassermann *et al*. [17] will be determined in a separate testing session at least one week before the experiment. Participants will perform a ramp test on a cycle ergometer until exhaustion. An electrocardiogram (ECG) will be performed and blood pressure will be monitored simultaneously as an ergospirometry. The identification of the VT2 is required in order to assess the defined workloads for the trials. Lean body mass will be determined using dual-energy x-ray absorptiometry (DXA).

### Outcomes

#### Primary outcomes

In addition to ANP and BNP, the primary outcomes are the respiratory exchange rate (RER) and the rating of perceived exertion (RPE). The RER specifies the ratio of carbon dioxide (CO_2_) eliminated to oxygen (O_2_) consumed. The RER depends on the metabolic substrate used for generating energy. Using stoichiometric equations, the RER can be applied to determine the amounts of carbohydrates and fatty acids metabolized. Energy production can also be reliably estimated in the same manner. The RPE method requires that a person subjectively rates how difficult the work is, using a numerical scale that is related to exercise intensity.

#### Secondary outcomes

Secondary outcomes are lactate, catecholamine (that is, adrenaline, noradrenaline, and dopamine), growth hormone, insulin and glycerol, all of which indicate changes in the metabolic process.

### Assessment of effectiveness and proof of evidence

#### Measurement of effectiveness

Effectiveness will be measured by the following methods:

•Gas-exchange open system, breath-by-breath-method (Viasys Jäger Master Screen CPX, PanGas AG, Dagmarsellen, Switzerland)

•ECG-monitoring by means of suction electrodes (Viasys Jäger Master Screen CPX, PanGas AG, Dagmarsellen, Switzerland)

•Continuous heart-rate monitoring (Polar-S-810 heart rate monitor)

•measuring of the blood pressure according to Riva-Rocci via inflatable cuff on the upper arm

•Rating of perceived exertion (Borg-scale)

•Sampling of blood (ANP, BNP, glycerol, FFAs, lactate, catecholamine (adrenaline, noradrenaline, dopamine), growth hormone, insulin, and glucose).

#### Proof of evidence

Proof of evidence will be provided by the following parameters:

•RER, VO_2_ and CO_2_

•ANP concentration (radioimmunoassy)

•Glycerol concentration (radiometric determination)

•Free fatty acids (FFAs) (enzymatic determination)

•Lactate (photometric determination)

### Assessment of safety

#### Safety parameters: measuring methods and times

Exclusion criteria for the ergospirometry are subjective disorders (stenocardia, dyspnea, dizziness, muscular exhaustion), variations in the ECG during the ergospirometry (ST-depression > 0.2 mV, ST-elevation > 0.2 mV, dysrhythmia), pathological changes in blood pressure (no rise or fall in blood pressure during the examination, blood pressure values >250/130 mm Hg) and a measured heart rate (HR) above the age-based maximum (HRmax = 220 – age in years).

The oxygen pulse as a correlate of the stroke volume is a relevant clinical safety parameter. When workload increases, a reduced stroke volume leads to stagnation of the oxygen pulse followed by a slow drop of the values measured. Therefore, the oxygen pulse is fundamental when estimating the myocardial function. The oxygen absorption will also be evaluated in regard to changes in the workload. Cardiovascular disease leads to low measured values, and performance limitations become observable. The respiratory reserve allows for estimation of pulmonary ventilation. Healthy subjects are not limited in their performance by pulmonary factors. The respiratory reserve is still sufficient (approximately 50% MVV when exercising at their maximum. Pulmonary diseases lead to approximation of the respiratory reserve to the MVV, indicating a pulmonary limit. Respiratory gases, ECG and blood pressure will be assessed, allowing for differentiated identification of cardiac reactions. In the event of a severe and life-threatening incident, the ethics committee and the sponsor will be informed.

Blood samples will be taken by laboratory assistants who are familiar with the operating procedures and safety standards. During the trial blood samples will be taken every 15 minutes (continuous endurance exercise) or after each exercise step (high-intensity intermittent endurance exercise). Moreover, one blood sample will be taken pre- and post-exercise. Viollier laboratories (in-house) will process and analyze the blood samples.

### Data collection

Data collection is described in detail in the Methods section.

### Statistical methods

Figures will be presented as means ± standard error of the mean (SEM). Differences in outcomes among the groups will be tested by analysis of covariance (ANCOVA). For statistical significance (*P* <0.05), multiple comparisons will be adjusted for using the Tukey test.

Our assumptions for the power calculation are mainly based on the results of Fenzl *et al*. [18] who recently reported an increase of ANP from 29.8 ± 3.4 pmol/l to 82.5 ± 8.3 pmol/l. Assuming an increase from 35 to 55 with a SD of 10, we would need eight patients in each group to achieve 90% power at the 1% significance level (two-sided test). With an assumed drop-out rate of two in each group, we need 20 persons in total.

Hormone values that are expected to rise during the recovery period of the exercise include catecholamines, ANP, BNP, glycerol and free fatty acids. Differences in these hormones between high-intensity intermittent exercise protocols compared to less intense protocols have not yet been analyzed; studies investigating intermittent bouts of exercise results were in contrast to moderate continuous exercise of the same duration. Different scores relative to the contribution of fat oxidation for repeated trials (77.6% ± 2.7%) versus single trials (62.1% ± 5.7%) were computed in the study of Goto *et al*. [11]. A test would require less than 10 subjects in each group, assuming a similar response to water immersion. Matsuo *et al*. [19] demonstrate that EPOC was greater when high-intensity interval training was conducted compared to aerobic types of exercise. For the power calculation, eight subjects in each group should be included into the study.

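### The trial is a two-period crossover, but the stated ANCOVA and sample size are written for parallel groups, so nothing shows that the within-man pairing or the period is used

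*Protocol article*

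**What the plan says.** On design, the Trial design section states: "The two testing trials will be performed according to a randomized crossover design". The Overview adds that "the tests will be conducted as repeated measurements, with 72 hours of separation time in between". Each man therefore contributes a continuous and an intermittent session.

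On allocation, the Trial design section says: "Subjects will be allocated to one of the two intervention groups according to a prepared randomization list". It does not mention sequence.

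On analysis, the Statistical methods section says "Differences in outcomes among the groups will be tested by analysis of covariance (ANCOVA"), sets the threshold as "For statistical significance (*P* <0.05"), and adds that "multiple comparisons will be adjusted for using the Tukey test". It names no covariate, subject, period or sequence term. Results are to be shown per condition: "Figures will be presented as means ± standard error of the mean (SEM").

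On size, the same section reasons: "Assuming an increase from 35 to 55 with a SD of 10". From this it derives eight patients per group for 90% power at a two-sided 1% level, allows two drop-outs per group, and reaches 20 in total. The later remarks on fat oxidation and EPOC also count subjects per group.

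**The concern.** In a two-period crossover the exercise protocols are conditions, and the only groups are the two sequences. A comparison among intervention groups, with a sample size per group, belongs to a trial in which each man does one protocol only.

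If the analysis follows that wording, a man's two sessions are handled as if they came from different men. Variation between men, which cancels in the within-man difference, stays in the error term. Real differences between the protocols can then be missed.

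Serial blood sampling adds a risk in the other direction. Samples are planned every 15 minutes or after each exercise step. If they enter as independent observations, the standard error becomes too small. The reader cannot tell which of these errors, if either, the final analysis would carry.

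**Working it through.** **1. The plan's own figure.** Inputs from Statistical methods: difference 55 − 35 = 20, SD 10, two-sided alpha 0.01, power 90%. The independent two-group normal formula gives

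n = 2(z₀.₉₉₅ + z₀.₉₀)² × SD²/Δ² = 2(2.576 + 1.282)² × 100/400 = 7.44, so 8 per group.

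Power at 8 per group: 20/(10 × √(2/8)) = 4; 4 − 2.576 = 1.424; Φ(1.424) = 92.3%. Total: (8 + 2) × 2 = 20. The stated figures are reproduced. With the exact t distribution, 8 per group gives 82.6% and 10 per group are needed.

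Eight also comes out of a paired t-test if 10 is the SD of a difference (88.3% power with 7 men, 95.1% with 8). In a crossover, however, that eight would be the total. Doubling it is parallel-group reasoning under either reading of the SD.

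**2. The within-man equivalent.** Let ρ be the correlation between a man's two sessions. The article does not give it, so a range is assumed. Taking 10 as the between-subject SD, the SD of the within-man difference is 10√(2(1 − ρ)), which is 14.14, 11.83, 10.00 and 7.75 at ρ = 0, 0.3, 0.5 and 0.7. With a period term (N − 2 degrees of freedom), alpha 0.01 and 90% power, the total number of men needed is 12, 10, 8 and 7.

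**3. Subject ignored, one value per session.** The standard error is SD√(2/n) instead of SD√(2(1 − ρ)/n), a ratio of 1/√(1 − ρ). The table takes 16 completers and nominal alpha 0.05. Type I error and power are simulated; the detectable difference is for 90% power and is approximate for the subject-ignoring test.

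| ρ | SE ratio | Actual type I error | Power at 0.5 SD: ignored / paired | Detectable difference: ignored / within-man |
|---|---|---|---|---|
| 0.3 | 1.20 | 2.1% | 24% / 35% | 11.0 / 10.4 |
| 0.5 | 1.41 | 0.8% | 21% / 47% | 10.4 / 8.8 |
| 0.7 | 1.83 | 0.1% | 17% / 67% | 9.7 / 6.8 |

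At ρ = 0 the type I error is 5.0%.

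**4. Each session's pre-exercise value as covariate, still no subject term.** Simulated type I error is 3.4% (ρ 0.5, pre-post correlation 0.5), 3.6% (0.7, 0.7) and 0.4% (0.7, 0.3). The covariate helps as far as it carries the man's stable level, and not otherwise.

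**5. Serial samples as independent rows.** Six samples per session are assumed, since the article gives no count. Simulated type I error, by between-session and within-session correlation:

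- 0.3, 0.5: 13.9%
- 0.3, 0.7: 24.1%
- 0.5, 0.7: 12.1%
- 0.5, 0.8: 18.0%
- 0.7, 0.8: 3.9%

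**6. The planned effect.** At a difference of 20 with SD 10, a subject-ignoring two-sample test on 16 values per condition has 99.7% power at alpha 0.01. The within-man analysis has at least 99.1% for any ρ of 0 or more.

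**7. Period.** Let π be the period effect. Without a period term, the mean within-man difference carries π times the difference in sequence sizes divided by the number of men. With two drop-outs per group, as assumed, the sequences are 8 and 8 and the bias is zero. With 10 and 6 it is (10 − 6)/16 = 25% of π, but all four drop-outs must then fall in one sequence.

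**The case against.** The article lists no model terms at all, not even the covariate, and a condensed article may leave these to the full plan. An ANCOVA with man and period as factors is a valid crossover analysis. The crossover is declared, the Overview speaks of repeated measurements, and the allocated group can be read as the sequence. A reader might infer that the analysis leaves out man and period; the text does not say so. This part of the objection stands.

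It does not remove the point. The section goes beyond silence: it makes a positive comparison among groups and counts patients and drop-outs per group throughout. The Overview's reference to repeated measurements describes how the tests are conducted, not how they are analysed.

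A reader might also infer that the test is far too conservative. That needs a within-man correlation the article does not give. At 0.3 the standard error is inflated by only 1.20, a pre-exercise covariate can remove much of the effect, and serial samples can reverse its direction. The Tukey adjustment makes serial samples relevant: with only two conditions it has nothing to adjust, so more than two means may be compared.

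The presentation as mean ± SEM is descriptive and not an error in the test. It merely does not show the precision of the paired contrast.

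**Conclusion.** The concern holds in this limited form: the stated test and sample size follow a parallel-group design that the trial does not have, and as worded the error rate is not controlled in either direction. With one value per session and subject ignored, the test is conservative whenever the within-man correlation is above 0. With serial samples treated as independent, it was anti-conservative in four of the five scenarios examined. All these sizes rest on assumed correlations, 16 completers and, for the serial case, an assumed six samples per session.

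Two stronger conclusions are not supported. The planned ANP comparison is not underpowered if 20 with SD 10 is the contrast between protocols; the loss falls on smaller effects and on other outcomes. That condition matters, because the article words the 20 as an increase, directly after citing an observed rise in ANP, and says that hormone differences between such protocols have not yet been analysed. Nor is a period bias established: under the plan's own drop-out assumption it is zero, and no period effect is quantified.

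**What to change.** In the Trial design section, state that men are randomised to sequence (continuous first or intermittent first).

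In Statistical methods, replace the comparison among groups with a within-man model for each outcome: exercise protocol and period as fixed effects, man as random effect, and that session's pre-exercise value as covariate. Where serial samples are analysed, add time and protocol-by-time, with correlation within session. Report the within-man difference between protocols with its 95% confidence interval.

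State whether the SD of 10 is between subjects or that of the within-man difference, and whether 20 is the difference between protocols. Restate the sample-size basis as a total number of men, with the assumed within-man correlation if one is needed.

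The cost is a few sentences. No new data are needed, the 20 men need not change on these inputs, and the article's status section says that recruitment has not begun.

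### The Tukey test, the only multiplicity adjustment named, does not control error across the four unranked primary outcomes; the 1% planning level that would do so is not used in the analysis

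*Protocol article*

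**What the plan says.** All references are to the protocol article.

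- **Comparison.** Trial design: "The two testing trials will be performed according to a randomized crossover design". Overview: "The two different exercise protocols will be compared". There are two conditions.
- **Primary outcomes.** The section of that name gives four, with no order or hierarchy: "In addition to ANP and BNP, the primary outcomes are the respiratory exchange rate (RER) and the rating of perceived exertion (RPE").
- **Analysis.** Statistical methods: "Differences in outcomes among the groups will be tested by analysis of covariance (ANCOVA"). The next sentence says that, for significance at P<0.05, "multiple comparisons will be adjusted for using the Tukey test".
- **Sample size.** The same section sizes the trial on ANP alone (35 to 55, SD 10) and asks for "eight patients in each group to achieve 90% power at the 1% significance level (two-sided test"). It then adds two drop-outs per group, for 20 men. It does not say why 1% was chosen or link it to the number of primary outcomes.

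**The concern.** Tukey's procedure protects a set of pairwise comparisons among the means of one outcome. The sentence just before it in the plan concerns differences between groups, and there are two groups, so for each outcome there is one pair and nothing to adjust. The multiplicity that the plan does create lies across four co-equal primary outcomes, where Tukey does not operate.

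The plan therefore states that multiple comparisons are adjusted for, while the error rate over its primary outcomes is left open. A reader of the results could take a P-value below 0.05 on one primary outcome as already adjusted. The same section also holds two significance levels, 1% for planning and 5% for analysis, with nothing to connect them.

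**Working it through.** **Inputs from the article.** Two protocols (Trial design, Overview); four primary outcomes (Primary outcomes); analysis level 0.05; planning level 0.01 two-sided, 90% power, difference 55 − 35 = 20, SD 10, 8 per group plus 2 drop-outs (Statistical methods). The correlations among outcomes are not given; the values below are assumptions.

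**1. The plan's sample size.** Normal approximation, two independent groups: n = 2 (SD/difference)² (z₁₋α/₂ + z₁₋β)² = 2 × (10/20)² × (2.576 + 1.282)² ≈ 7.4, so 8 per group, and (8 + 2) × 2 = 20. The stated figure is reproduced. With the noncentral t distribution, 8 per group gives 82.6% power at 1% and 10 per group gives 93.0%.

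**2. Tukey with two means.** The critical value for a pairwise difference is the studentized-range quantile divided by √2. At an overall 5%:

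| df | Tukey, 2 means | Unadjusted t |
|---|---|---|
| 14 | 2.1448 | 2.1448 |
| 18 | 2.1009 | 2.1009 |
| 19 | 2.0930 | 2.0930 |

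For the comparison of the two protocols there is no adjustment.

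**3. Tukey over more than two means.** At df 14 the critical value rises to 2.617 for 3 means and 2.907 for 4. Applied to time points, Tukey does adjust, but within one outcome at a time.

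**4. Error across the four primary outcomes, each at 5%.**
- Independent: 1 − 0.95⁴ = 0.185. Upper bound under any dependence: 4 × 0.05 = 0.20.
- Simulated, four equally correlated normal outcomes, all null hypotheses true: 17.4% at correlation 0.3, 15.6% at 0.5, 11.4% at 0.8.
- On the time-point reading, Tukey holds each outcome's own set of comparisons to 5%. Four such sets, if independent, can still reach 18.5%.

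**5. The same at the planning level.** 1 − 0.99⁴ = 0.039 if independent; upper bound 4 × 0.01 = 0.04.

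**6. Does the level mismatch cost power?** No. At 5% the same inputs need 2 × (10/20)² × (1.960 + 1.282)² ≈ 5.3, so 6 per group. With 8 per group the noncentral-t power at 5% is 96.0%.

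**7. Power for ANP at the first Holm step, 0.05/4 = 0.0125.** Normal approximation: 8 per group still suffices. Noncentral t: 85.2% with 8, 90.6% with 9, 94.2% with 10 per group.

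**The case against.** **Tukey may have been meant for the repeated samples.** The Overview describes repeated measurements, and Assessment of safety schedules blood sampling every 15 minutes or after each exercise step, plus samples before and after exercise. Over those time points there are more than two means. This stands to the extent that a reader who infers that Tukey has no effect anywhere goes too far: that holds only for the two-protocol comparison. But Statistical methods does not name time points, and this reading leaves the four outcomes uncovered.

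**The 1% may already be the allowance for four outcomes.** It would work as one (step 5), but the article does not say so, and its analysis level is 0.05. A reader might also infer that planning at 1% and testing at 5% leaves the trial underpowered. It does not (step 6). The fault is that the levels are not reconciled.

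**The claim may be joint.** The first aim asks for higher natriuretic peptides and also a higher lipolysis marker. If all must be shown, testing each at 5% does not inflate error for that claim. This is fair, and nothing in the article says that one significant outcome out of four would be reported as confirmation. Yet no joint rule is stated, and the aim does not match the primary set: the Intervention section names ANP, BNP and glycerol, glycerol is secondary, and RER and RPE are not in the aim. Nor can a joint power be had by multiplying the stated 90%: that figure is for ANP at 1%, and the article gives no effect size and SD for BNP or glycerol.

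**Such detail belongs in an analysis plan.** Silence could be left to one. Here the protocol itself names a method, and that method does not address its primary outcomes.

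**Conclusion.** The point holds in this form: the only adjustment named does not control error across the four primary outcomes on either reading of the Tukey sentence, and for the two-protocol comparison it is identical to no adjustment.

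The chance of at least one false positive is 18.5% under independence and about 11% to 17% at assumed correlations of 0.8 to 0.3, against a nominal 5%. These figures assume that all four null hypotheses are true, that each outcome is tested at 5%, and that any one significant result could be claimed. ANP and BNP are probably correlated, so the true value is likely below 18.5%. The planning level of 1% would hold it at or below 4%, but is not carried into the analysis.

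**What to change.** In Statistical methods, replace the Tukey sentence with: the four primary outcomes (ANP, BNP, RER, RPE) are tested with Holm's procedure at an overall two-sided 5%. The ordered P-values are compared with 0.05/4 = 0.0125, 0.05/3 = 0.0167, 0.05/2 = 0.025 and 0.05, stopping at the first that fails. Keep Tukey only for time-point comparisons within an outcome, if that was the intent, and say so. In the power paragraph, state how the 1% level relates to this rule. The stated primary outcomes stay as they are.

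The cost is a short text change, before recruitment according to Trials status, and a stricter threshold on some primary outcomes. For ANP on the plan's two-group inputs, power at the strictest step is 94% with 10 per group and 85% with 8. The first step is looser than the 1% already used for planning, so the planned total of 20 need not change on this account. Power for BNP, RER and RPE cannot be worked out, because the article gives no effect sizes and SDs for them.
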